### 6.7.7 Evaluation of urinary discomfort

The IPSS (*International Prostate Score Symptom)* is a self-administered questionnaire whose French version has been validated (appendix 12). The IPSS is made of 7 questions evaluating the severity of urinary symptoms. The questionnaire has been developed for the patient’s self-evaluation. Responses are checked from 0 to 5. Each question has six possible responses quantifying in increasing fashion the severity of symptoms. The total score can consequently be added, from 0 to 35 points (asymptomatic to very symptomatic). Patients can be classified as follows:

0-7: few symptoms

8-19: moderate symptoms

20-35: severe symptoms

##

## 6.8 Statistical analysis and determination of the number of patients

### 6.8.1 Data management

Data input and management shall be performed by the Centre Oscar Lambret Biostatistics Unit. A study-specific database shall be created, tested and validated before data entry. This data base shall be developed by the “Data Treatment Center of the North-West Canceropole, authorized by the INCa” with the Capture System (CLINSIGHT). This software program has been designed for the global management of clinical studies, and meets the regulatory requirements associated with this type of study.A data validation plan shall be defined, providing a detailed description of the controls required for each variable, along with the list of obvious corrections allowed.

Questionnaires shall be validated on receipt and shall be independently entered twice. After comparing the two entries and generating a single database, the data shall be checked by the team in charge of data management using the error messages generated by the validation programs. Any obvious errors shall be corrected. Other errors, omissions or inconsistencies shall be stated on correction request forms that shall be sent to the investigating physician for resolution. Once the Biostatistics Unit receives the investigating physician's response, the corrections shall be added to the database.

The database is locked after final quality control, then exported to the SPSS statistical software using an automated and validated procedure.

### 6.8.2 Statistical analysis

The initial characteristics of included patients will be presented in the form of summary tables. Continuous variables will be summarized by conventional descriptive statistics parameters (median and outlying values, mean and standard deviation when necessary). Category variables will be presented in the form of contingency tables (absolute frequency and percentage of each modality), additionally stating the number of missing data, along with the 95% confidence interval.

Subject inclusion and exclusion criteria will be checked against data entered into the case report forms when possible. Any deviations from the protocol will be documented.

Survival will be analyzed by the Kaplan-Meier nonparametric method.

### 6.8.3 Determination of the number of subjects

The number of patients required for this study was calculated using the single step Fleming method with the following hypotheses :

P0 = 85% (level of patients without any toxicity below which the method would provide no

advantage)

P1 = 95% (level of patients without toxicity expected from the proposed methods)

= 5%

= 10% , i.e. a power of 90%

To meet these conditions, the Fleming formula requires 76 evaluable patients to be included (38 by CyberKnife and 38 by linear accelerator). The study's goal will be considered achieved if, of the 76 evaluable patients, at least 70 present no grade 3-4 toxicity according to the NCI scale.

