# 5 STUDY OBJECTIVES

## 5.1 Primary objective

- Evaluate urinary and rectal toxicity according to the NCI-CTCAE v3.0 scale of conventional radiotherapy to 46Gy (prostate and seminal vesicles) followed by a 3 x 6Gy stereotactic boost (prostate only) administered either with CyberKnife or with a linear accelerator

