#### *Serious adverse event - expected (SAE-E)*

A SAE-E is an event already mentioned in the results of studies with this type of treatment :

- Rectitis +/- hemorrhagic
- Cystitis +/- hemorrhagic

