#### Intensity criteria

The intensity criterion must not be confused with the seriousness criterion, which serves as a guide to define declaration obligations.

The intensity of events will be estimated according to the NCI-CTCAE version 3.0 classification (toxicity grade 1 to 5). The intensity of unlisted adverse events in this classification will be estimated according to the following qualities :

**Mild** (grade 1): does not affect the patient's daily activity

**Moderate** (grade 2): disturbs the patient's daily activity

**Severe** (grade 3): prevents the patient's daily activity

**Very severe** (grade 4): requires reanimation measures / life threatening

**Death** (grade 5):

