| **SEXUAL/REPRODUCTIVE FUNCTION** | | | | | | | | | | | | | |
| Breast volume/hypoplasia | Breast | | | Minimal asymmetry; minimal hypoplasia | Asymmetry exists, ≤1/3 of the breast volume; moderate hypoplasia | | Asymmetry exists, >1/3 of the breast volume; severe hypoplasia | | — | | — | | |
| REMARK: Breast volume is referenced with both arms straight overhead. | | | | | | | | | | | | | |
| Erectile dysfunction | Erectile dysfunction | | | Decrease in erectile function (frequency/rigidity of erections) but erectile aids not indicated | Decrease in erectile function (frequency/rigidity of erections), erectile aids indicated | | Decrease in erectile function (frequency/rigidity of erections) but erectile aids not helpful; penile prosthesis indicated | | — | | — | | |
| Ejaculatory dysfunction | Ejaculatory dysfunction | | | Diminished ejaculation | Anejaculation or retrograde ejaculation | | — | | — | | — | | |
| Gynecomastia | Gynecomastia | | | — | Asymptomatic breast enlargement | | Symptomatic breast enlargement; intervention indicated | | — | | — | | |
| ALSO CONSIDER: Pain – *Select.* | | | | | | | | | | | | | |
| Infertility/sterility | Infertility/sterility | | | — | Male: oligospermial/low sperm count Female: diminished fertility/ ovulation | | Male: sterile/azoospermia Female: infertile/ anovulatory | | — | | — | | |
| Irregular menses (change from baseline) | Irregular menses | | | 1 – 3 months without menses | >3 – 6 months without menses but continuing menstrual cycles | | Persistent amenorrhea for >6 months | | — | | — | | |
| Libido | Libido | | | Decrease in interest but not affecting relationship; intervention not indicated | Decrease in interest and adversely affecting relationship; intervention indicated | | — | | — | | — | | |
| Orgasmic dysfunction | Orgasmic function | | | Transient decrease | Decrease in orgasmic response requiring intervention | | Complete inability of orgasmic response; not responding to intervention | | — | | — | | |
| Sexual/Reproductive Function – Other (Specify, ) | Sexual – Other (Specify) | | | Mild | Moderate | | Severe | | Disabling | | Death | | |
| **VASCULAR** | | | | | | | | | | | | | |
| Phlebitis (including  superficial thrombosis) | Phlebitis | | | — | Present | |  | |  | | Death | | |

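### Section 6.8.3 defines its hypotheses and its success rule on different toxicity events, and neither matches the urinary and rectal primary endpoint

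*Protocol*

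**What the plan says.** Section 6.8.3 describes a single-step Fleming design. Its null hypothesis is "P0 = 85% (level of patients without any toxicity below which the method would provide no" advantage, and its alternative is "P1 = 95% (level of patients without toxicity expected from the proposed methods". Alpha is 5% and beta is "10% , i.e. a power of 90"%. The design needs 76 evaluable patients, and the goal is met if "at least 70 present no grade 3-4 toxicity according to the NCI scale".

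The primary objective in section 5.1 is to "Evaluate urinary and rectal toxicity according to the NCI-CTCAE v3.0 scale". The Synopsis gives the primary assessment criterion as urinary or rectal toxicity on the same scale. Neither states a grade threshold.

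Under Intensity criteria in section 6.7.1, events are graded by the "NCI-CTCAE version 3.0 classification (toxicity grade 1 to 5"), with grade 5 labelled death. Appendix 10 also has a separate grade 5 column.

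**The concern.** Three descriptions of the primary event stand in the protocol and they are not the same.

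- **Grade.** P0 and P1 speak of no toxicity. The rule speaks of no grade 3-4 toxicity.
- **Organ.** The objective and criterion are urinary and rectal. The rule covers anything on the NCI scale.
- **Upper end of the scale.** The rule names grades 3 and 4 and leaves out grade 5.

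This is the trial's only go/no-go rule. If it is applied as written, two kinds of patient are misclassified relative to the objective: one whose only severe event is recorded as grade 5 (scored a success), and one whose only grade 3 event lies in another organ (scored a failure). If it is applied by intent, someone has to decide what the intent was, possibly after seeing the data.

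**Working it through.** **1. Reproduce the plan's figures.** Inputs from section 6.8.3: P0 = 0.85, P1 = 0.95, alpha = 0.05, power = 0.90. Sidedness is not stated; one-sided is the choice that reproduces the sample size.

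n = [(z_alpha × √(P0(1−P0)) + z_beta × √(P1(1−P1))) / (P1 − P0)]²

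= [(1.645 × 0.3571 + 1.282 × 0.2179) / 0.10]² = 75.1, rounded up to 76. A two-sided alpha would give 95.9.

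Cut-off: 76 × 0.85 + 1.645 × √(76 × 0.85 × 0.15) = 64.6 + 1.645 × 3.113 = 69.7, so 70.

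Exact check with X ~ Binomial(76, p):

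- P(X ≥ 70 | 0.85) = 0.0497
- P(X ≥ 70 | 0.95) = 0.9144

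Both figures in the plan are confirmed. They describe the rule only when p is the probability of the event being counted.

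**2. Set the event definitions side by side.**

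| Place | Grades | Organs |
|---|---|---|
| P0, P1 (6.8.3) | any (no threshold) | not stated |
| Success rule (6.8.3) | 3-4 | not stated |
| Objective (5.1), criterion (Synopsis) | no threshold | urinary, rectal |
| Scale (6.7.1) | 1 to 5, 5 = death | all |

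No other section says which definition governs the count.

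**3. Grade 5, by counting.** Suppose 6 patients have grade 3-4 toxicity and 3 others have toxicity recorded only as grade 5. The literal rule counts 76 − 6 = 70, so the goal is met. Patients free of grade 3 or worse number 76 − 9 = 67, which is below 70. The rate of grade 3 or worse is 9/76 = 11.8%.

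**4. Grade 5, by probability.** The protocol gives no such rate, so these are assumptions. Take a true rate of 85% free of grade 3 or worse, and let a fraction d of all patients have a grade-5-only event that is counted as a success. The counted rate is then 0.85 + d.

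| d | P(X ≥ 70) |
|---|---|
| 0 | 0.050 |
| 1% | 0.079 |
| 2% | 0.121 |
| 3% | 0.179 |

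**5. Other organs, by probability.** These rates are also assumed. Take a true rate of 95% free of urinary and rectal grade 3 or worse, and let a further fraction e of patients have only an other-organ grade 3 event. The counted rate is 0.95 − e.

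| e | P(X ≥ 70) |
|---|---|
| 0 | 0.914 |
| 2% | 0.718 |
| 3% | 0.593 |

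Erectile dysfunction is the plausible route. Appendix 10 has a grade 3 level for it, and section 7.2.4 names altered sexual function as the main toxicity to expect when the irradiated volume extends too low. Section 5.2 treats sexual dysfunction as a separate secondary objective.

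**The case against.** **The wording is shorthand.** Only one decision rule is written and it states its grade. A 95% rate free even of grade 1 events is implausible, since section 4.3.5 reports grade 1-2 rectal toxicity in comparable series. The rule also serves a criterion already restricted to urinary and rectal events. As a guess at intent this is reasonable: grade 3 or worse, urinary or rectal, was probably meant. It does not remove the defect, because the text never says so and the error rates depend on it.

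**Toxic deaths would not pass unnoticed.** A reader might infer that the plan lets toxic deaths through as successes in general. The documents do not support that. The gap needs a death with no grade 3-4 event also recorded, because an earlier grade 3-4 record already makes the patient a failure. The series cited in section 4.3.5 mention no deaths. Deaths are also covered by the stopping rule in section 6.8.4 and by the committee in section 8.5. Neither of these classifies a patient for the success count, however. The stopping rule covers deaths within 3 months of the last boost session, and its listed fractions end at 18 patients.

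**The organ examples are weak.** This is partly right. Appendix 10 lists "Male: sterile/azoospermia" at grade 3, but no scheduled visit includes a semen analysis, so that item would hardly be recorded. Erectile dysfunction remains a realistic example.

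**Appendix 10.** A reader might infer that the appendix leaves the main events ungradable, since "Cystitis +/- hemorrhagic" is a named expected event without a row of its own. That goes too far. Rectal mucositis, ulcer, obstruction and hemorrhage are listed with specific grades. Bleeding at other sites has a transfusion-based row, and the need for a catheter is grade 3 under urinary frequency. The governing scale is CTCAE v3.0 itself. What stands is small: the extract has no named rows for cystitis, urinary retention or urinary incontinence.

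**Conclusion.** The inconsistency is real and sits in the primary decision rule. The sample size and cut-off are not in error: 76 and 70 are right for 85% against 95%, with exact one-sided alpha 0.0497 and power 0.914. Those properties hold only if the two rates refer to the event that is counted, and the protocol does not say that they do.

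The size of the effect cannot be fixed from the document. Under the assumed rates above, the chance of wrongly declaring success could rise from 0.050 to between 0.079 and 0.179, or power could fall from 0.914 to between 0.718 and 0.593. These two effects work in opposite directions. It would therefore be wrong to infer that correcting the rule can only make the result less favourable: counting grade 5 can remove successes, while excluding other organs can add them.

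**What to change.** Use one event in P0, P1 and the rule: patients free of grade 3 or higher (3, 4 or 5) urinary or rectal toxicity on CTCAE v3.0, with success if at least 70 of 76 evaluable patients are free. Report other-organ toxicity descriptively.

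The sponsor should confirm that 85% and 95% were meant for that event. If so, the sample size and cut-off do not change. If they were meant for freedom from any toxicity, the rates must be restated for the counted event and the design recomputed.

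Two smaller additions would complete the definition. State that the endpoint is graded on the complete CTCAE v3.0, given the named rows missing from the extract. Also state the observation window, since the Synopsis dates the six-month acute period from the start of radiotherapy and section 6.7.1 dates it from the end.

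The cost is a few lines of protocol wording, provided the sponsor confirms the rates.

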### 6.8.4 Criteria for termination of the study

The study will be terminated if :

- a Grade 4 toxic event is observed according to the NCI scale,
- or a death in the 3 months following the last session of hypofractionated stereotactic boost irradiation

**in 2/3 or 3/8 or 4/11 or 5/18 patients.**

# 7 TREATMENT

## 7.1 Patient enrollment

An inclusion request form will be completed by the investigator in order to ensure that the patient fulfils ALL selection criteria. The investigator must provide the information letter to the patient and have him sign the consent form making explicit its free and informed consent.

BEFORE INITIATING TREATMENT, the investigator must fax the inclusion request form to the Coor-dination Center of the study:

Clinical Research Integrated Unit / Promotion Section

Centre Oscar Lambret – Lille

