#### Steps to take

The investigator informs the Integrated Clinical Research Unit of all **Serious Adverse Events** whether or not they can be attributed to the research, which occur during the study or in the 3 months following the first irradiation session.

All late Serious Adverse Events (occurring after this 3 month period) considered as being reasonably related to the protocol treatment or to the research, must be declared without time limitation.

Declarations will be submitted by fax to the Clinical Research Unit using the "***serious adverse event notification***" form (appendix 10), documented in the most precise manner possible, dated and signed, within **24 working hours** of their observation, to :

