## 8.5 Independent monitoring committee

An independent monitoring committee for the trial will be established in order to guarantee protection of the patients, to ensure that the trial is conducted in an ethical fashion, to evaluate the risk/benefit ratio of the trial and to ensure the review of the scientific results during and at the end of the trial. The monitoring committee will meet 3 months after the inclusion of the ten fisrst patients and then on a regular basis.

Committe membership to be confirmed :

Two radiation oncologists : [name], [name]

An urologist : [name]

A medical physicist : [name]

- A methodologist : [name]

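### The numerical stopping rule ends at patient 18 and ignores grade 3 toxicity, so inclusions can continue after the primary goal has become unreachable

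*Protocol*

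**What the plan says.** Protocol section 6.8.3 uses a single-step Fleming design. The unacceptable level is given as "P0 = 85% (level of patients without any toxicity below which the method would provide no" advantage and the expected level as "P1 = 95% (level of patients without toxicity expected from the proposed methods"). The error rates are 5% and "10% , i.e. a power of 90"%. The goal is met if, of 76 evaluable patients, "at least 70 present no grade 3-4 toxicity according to the NCI scale".

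Section 6.8.4 lists two stopping events. One is that "a Grade 4 toxic event is observed according to the NCI scale"; the other is a death within 3 months of the last boost session. The section closes with the boundary: "in 2/3 or 3/8 or 4/11 or 5/18 patients". No fraction is given beyond 18 patients, and grade 3 is not mentioned.

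Sections 7.4 and 8.5 set up an independent committee with a risk/benefit remit. Section 8.5 fixes its first meeting: "The monitoring committee will meet 3 months after the inclusion of the ten fisrst patients". Later meetings are described only as regular. Neither section gives it a numerical criterion.

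**The concern.** The success criterion and the stopping rule count different events over different numbers of patients. Success depends on grade 3-4 toxicity across all 76 patients. Stopping depends on grade 4 toxicity or early death, with boundaries only up to patient 18. The remaining 58 patients (58/76 = 76%) are entered under no numerical rule, and no number of grade 3 events at any point obliges anyone to pause.

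At stake is exposure without purpose: patients could be irradiated in a study that can no longer reach its own goal, and whether anyone notices depends on when the committee next meets. This is not detail left to a statistical analysis plan. The protocol states a complete termination rule, and that rule does not connect to the protocol's own primary criterion.

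**Working it through.** **Inputs.** From section 6.8.3: P0 = 0.85, P1 = 0.95, alpha = 0.05, beta = 0.10, N = 76, success at 70 or more. From section 6.8.4: boundaries 2/3, 3/8, 4/11, 5/18. The fractions are read as the shared ending of both stopping events.

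**1. The plan's own sample size.** n = [(z_alpha·√(P0(1-P0)) + z_beta·√(P1(1-P1))) / (P1-P0)]². With one-sided 5%, n = 75.1, rounded up to 76. A two-sided 5% gives 96 and does not match. Exact binomial for 70 or more of 76: alpha = 0.0497, power = 0.914. The design reproduces.

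**2. When the goal is lost.** At most 76 - 70 = 6 patients may have grade 3-4 toxicity. With the 7th, at most 69 can be free of it, and 69 < 70.

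**3. Chance that the stopping rule ever fires.** Exact binomial recursion over patients 1 to 18, removing at each boundary the paths that have reached it. For a true grade 4/death rate of 15%:

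- By patient 3: P(2 or more of 3) = 3·0.15²·0.85 + 0.15³ = 0.0608
- First reached at 8: 0.0699
- First reached at 11: 0.0142
- First reached at 18: 0.0502
- Sum: 0.195

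| True grade 4/death rate | P(rule fires) |
|---|---|
| 5% | 1.2% |
| 10% | 7.1% |
| 15% | 19.5% |
| 20% | 37.1% |
| 25% | 56.0% |
| 30% | 72.6% |

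Checking after every patient gives the same figures. If all toxicity is grade 3 and no early death occurs, the probability is 0. The documents do not say what share of grade 3-4 toxicity would be grade 4. If 10% to 20% is assumed, total toxicity of 15% means a grade 4 rate of 1.5% to 3%, and the rule fires in about 0.1% to 0.4% of trials.

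**4. When the goal is lost at the design's own unacceptable rate.** With 1 - P0 = 15% grade 3-4 toxicity, P(7 or more of 76) = 1 - 0.0497 = 0.950. The patient number of the 7th case is negative binomial. The probability that it has occurred is 0.497 by patient 44 and 0.522 by patient 45, so the median is 45. Patients left: 76 - 45 = 31. Averaging only over trials that do reach a 7th case also gives about 31.

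**5. Allowing for delay.** Step 4 treats toxicity as known when the patient enters. The synopsis plans 76 patients over 36 months, about 2.1 per month. If toxicity becomes known about 5.7 months after inclusion (an assumption: up to 82 days to the last boost, then the 3-month visit), about 5.7 × 2.1 = 12 more patients have entered by then. That leaves about 31 - 12 = 19. Toxicity seen earlier, at the weekly or pre-boost assessments, leaves more than 19; late toxicity leaves fewer.

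**The case against.** The strongest reply is that this is a design choice. A single-step design promises no interim futility look, a rule for life-threatening events need not mirror the success criterion, and full accrual serves the 3-year secondary objectives. The committee exists to protect patients and can recommend stopping. Much of this stands: the documents do not show that accrual would continue, only that nothing numerical would halt it. What remains is that no one is obliged to look when the goal is lost.

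A reader might infer four stronger points that the documents do not support:

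- **That the rule accepts a rate above 15% because 4/18 = 22% passes.** This compares an observed proportion with a true rate. At a true 15%, four or more of 18 occurs with probability 28%.
- **That deaths counted by section 6.8.4 go unreported.** Serious adverse events are reportable if they fall within the period "which occur during the study or in the 3 months following the first irradiation session". The first part of that wording covers a death within 3 months of the last boost. The later clause on late events makes the window ambiguous, so the two sections could be reconciled, but no missed death is shown.
- **That the first committee meeting comes too early.** Moving it to 3 months after the last boost would only delay independent review.
- **That some 53 patients would be treated needlessly.** That figure needs a 30% grade 3-4 rate, twice the design's unacceptable rate, and toxicity known at entry.

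The wording of section 6.8.4 also leaves some doubt. If the fractions qualified only deaths, a single grade 4 event would stop the study and the table above would not apply. That is the less natural reading, and the grade 3 gap would remain under it.

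**Conclusion.** The concern holds in a limited form. The only numerical stopping rule covers 18 of 76 patients and omits a toxicity grade that decides the primary result, so inclusions can continue after the 7th grade 3-4 case has made 70 of 76 unreachable. At a true 15% rate this point is reached with probability 0.95, typically around patient 45. About 31 patients then remain as an upper estimate, or about 19 under the delay assumed above. The rule itself is a weak safeguard: even if grade 4 or early death alone ran at 15%, it would fail to fire about 80% of the time.

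These figures rest on the fractions applying to both stopping events, on independent patients with a constant rate, and on reading P0 as the level free of grade 3-4 toxicity, as the success criterion does. They show a missing trigger, not that the committee would fail to act.

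**What to change.** Add to section 6.8.4 that, when the 7th evaluable patient with toxicity counted by the section 6.8.3 success criterion is recorded, inclusions are suspended and the committee is convened, because 70 of 76 can no longer be reached. Use exactly the count in section 6.8.3. A trigger defined on a different set of events, such as urinary or rectal toxicity only, would not coincide with the point at which the goal is lost.

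State also whether grade 4/death monitoring continues after patient 18, make explicit that the fractions apply to both events if that is meant, and give the rule's operating characteristics. Any extended boundary is for the sponsor to set. If the serious adverse event window is clarified alongside section 6.8.4, leave the first committee meeting no later than now.

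The cost is a short amendment and matching committee wording. The trigger acts only when the goal has already failed, so alpha (0.0497) and power (0.914) are unchanged. The downside is less precise secondary endpoints if accrual ends early.
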